**Primary outcome measures**					

Fatigue	Checklist Individual Strength (CIS; domain: fatigue) [47]	X	X	X	X

Daily activity performance	Sickness Impact Profile 68 (SIP-68; domains: mobility range, mobility control, social behaviour) [61]	X	X	X	X

HRQoL	Medical Outcome Study 36-Item Short-Form Health Survey (SF-36) [52]	X	X	X	X

**Secondary outcome measures**					

***ICF: Body functions***					

Pain	Visual Analogue Scale (VAS)	X	X	X	X

Emotional states	Profile of Mood States (POMS) [62,63]	X	X	X	X

Sleep disturbances	Nottingham Health Profile (NHP; domain: sleep) [64]	X	X	X	X

Cardio-respiratory fitness	Submaximal exercise test with cycle ergometer	X	X	X	X

Neuromuscular capacity	Fixed dynamometry and electrical stimulation	X	X	X	X

***ICF: Activities/Participation***					

Physical activity level in daily life	Activity Monitor (StepWatch, Cyma, Seattle, WA) on 7 consecutive days	X	X	X	X

Perceived participation	Impact on Participation and Autonomy Questionnaire (IPA) [65]	X	X	X	X

Functional Capacity	Timed-Up-and-Go test (TUG) [66] and 2-minute walk test (2-MWT) [67]	X	X	X	X

***ICF: Personal Factors***					

Illness cognitions	Illness Cognitions Questionnaire (ICQ) [51]	X	X	X	X

Coping	Coping Inventory for Stressful Situations (CISS-21) [68]	X	X	X	X

General Self Efficacy	General Self Efficacy Scale (ALCOS-16) [69]	X	X	X	X

**Effect Modifiers**					

***General effect modifiers***					

Demographic variables (age, gender, education, ethnicity, social-economical status)		X			

PPS main complaints	Polio Problem List (PPL) [9]	X	X	X	X

PPS disease severity	Medical Research Council scale (MRC) [26]	X			

Co-morbidity	Cumulative Illness Rating Scale (CIRS) [70]	X	X	X	X

Serum creatine kinase activity	Venipuncture	X *	X	X	X

***ICF: Environmental factors***					

Social support	Social Support Inventory (SSL-D) [60]	X	X	X	X

HRQoL (partner)	Medical Outcome Study 36-Item Short-Form Health Survey (SF-36) [52]	X	X	X	X

Coping (partner)	Coping Inventory for Stressful Situations (CISS-21) [68]	X	X	X	X

Caregiver Strain (partner)	Caregiver Strain Index (CSI) [71]	X	X	X	X

**Economic evaluation**					

HRQoL	EuroQol-5D [41]	X	X	X	X

Resource use	Cost diaries	X	X	X	X

* In the exercise group two extra blood samples will be obtained at 5 and 10 weeks.

T1; pre-treatment, T2; post-treatment, T3; short-term follow-up, T4; long-term follow-up.

#### Cardio-respiratory fitness

Subjects will perform a submaximal exercise test on a cycle ergometer (Lode Corival, Groningen, The Netherlands). The test starts with unloaded pedalling for three minutes, followed by a 10 Watt increment every single minute and will be terminated if one of the following occurs: (1) achieving 80% HRR or, (2) pedalling frequency dropping below 60 rpm, or (3) not being able to continue the test for any reason. The same workload protocol will be applied at the follow-up measurements. Throughout the test, gas exchange variables (COSMED K4b^2^, Rome, Italy) and heart rate will be measured continuously. Cardio-respiratory fitness will be determined based on changes in heart rate and gas exchange variables.

#### Neuromuscular capacity

Maximal voluntary contraction (MVC) of the quadriceps muscle will be measured isokinetically between 90° and 30° knee flexion using a fixed dynamometer (Biodex System 3, New York, USA). To determine MVC, subjects will perform three maximal-effort knee extensions at an angular velocity of 60°/sec. The highest value of peak torque (Nm) will be used for the analyses.

In addition, under isometric conditions, voluntary activation (VA) will be measured with a modified superimposed stimulation technique [34]. The quadriceps muscle will be electrically stimulated transcutaneously with surface electrodes placed over the proximal and distal part of the anterior thigh and using a computer-controlled constant current stimulator (Digitimer DSH7, Welwyn garden City, UK). A triplet (pulse train of three 200 μs pulses applied at 300 Hz with a supramaximal stimulation current) will be superimposed on a 3-4s maximal isometric knee extension at 60° knee flexion. An identical stimulation will be delivered to the relaxed quadriceps muscle to evoke a resting (control) triplet. Voluntary activation will be calculated by the following formula:

Fatigability of the quadriceps muscle will be determined by fatiguing the muscle by a series of electrically stimulated contractions. The current will be reduced such that a single tetanus at 150 Hz evokes approximately 30-50% of maximal isometric strength. A series of trains of 50 Hz stimulation (duration 1000 ms, with 1000 ms between trains) will be applied for a period of 300 seconds (150 contractions in total). Recovery of fatigue will be monitored by applying the same 50 Hz train (1000 ms duration) at different times (15 sec up to 3 min) after the end of the protocol. Changes in force, maximal rate of force rise and half relaxation time will be determined. These parameters will be expressed as a percentage of the values obtained in the first contraction of the protocol to correct for differences in muscle strength.

#### Adverse events

All adverse events reported spontaneously by the participants or observed by the therapists will be recorded. All adverse events will be followed until they have abated, or until a stable situation has been reached.

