In current practice, rehabilitation management is the mainstay of treatment for PPS. Rehabilitation aims to improve patients' capacities to perform activities of daily living and adapt performance (i.e. actual behaviour) to the available capacities. We expect that a reduction of the imbalance between patients' capacities and performance will lead to a reduction in fatigue and improvement in activities and HRQoL. There are two possible approaches to achieve this goal; exercise therapy and cognitive behavioural therapy (CBT). However, evidence to support the effectiveness of either approach is still limited.

The insufficient evidence to support exercise consists of contradictory and incomplete information in the literature. On the one hand, PPS patients are advised to avoid muscular overuse and intensive training as this could worsen symptoms such as muscle weakness and fatigue and provoke a further loss of muscular strength [1]. On the other hand, physically active PPS patients were found to have less symptoms of fatigue than sedentary patients [13]. It is unclear whether symptoms of fatigue are cause or result of physical inactivity. A systematic review on exercise therapy for neuromuscular diseases included ten studies on muscle strengthening exercises and aerobic exercises in PPS of which five demonstrated significant positive effects on muscular strength and aerobic capacity without generating any adverse effects. However, all these studies had to be qualified as having insufficient or limited methodological quality [14]. This led to the conclusion that there is insufficient evidence for the effectiveness of exercise for patients with PPS and that future, preferably multi-centre, studies are needed. A recent study on the short-term effectiveness of home- and hospital- based aerobic exercise showed improvement on fatigue and quality of life [15]. However results were not compared with a control group and long-term effectiveness was not evaluated in this study.

There is broad evidence for the effectiveness of CBT in reducing fatigue in chronic fatigue syndrome, fatigued post cancer survivors and multiple sclerosis [16-19]. However, there are no studies of CBT for fatigue in PPS.

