### Randomization and blinding

Patients will be assigned to the rehabilitation centre that is nearest to their home village. Randomization will be stratified per centre. Patients fulfilling both inclusion and exclusion criteria will be randomized to one of three groups: (1) exercise therapy + usual care, (2) CBT + usual care, or (3) usual care. The randomization scheme is computer-generated and will be done by creating random blocks of sequences with variable block sizes of 3 and 6. The investigator who will perform the randomization will inform the patient and, in case of allocation to exercise therapy or CBT also the therapist of the group allocation.

The investigators that are responsible for the inclusion will be blinded. Outcomes will be assessed by blinded and independent outcome assessors. At the beginning of the assessment patients will be instructed not to reveal their group allocation to the investigators. To evaluate the success of blinding, the investigator will be asked at each measurement, to guess the treatment assignment of the patient, with options 'CBT', 'exercise therapy', 'usual care only' and 'unknown'. Analyses will be performed blinded for treatment allocation.

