### Interventions

#### Usual care

The patients in the control and intervention groups will all receive usual care. Usual care for PPS patients may include usage of assistive devices, orthoses, physical therapy, and medication. Patients will not be restricted in their activities. Co-interventions will be monitored throughout the study.

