#### Exercise therapy

Exercise therapy is designed specifically to enhance physical capacity. The intervention has a duration of 16 weeks and consists of (1) a home-based aerobic training program three times weekly and a (2) supervised group training consisting of muscle strengthening and functional exercises once a week. The therapy will be supervised by specifically trained physiotherapists. An unblinded member of the project group will supervise the therapists and perform integrity checks on each treatment location.

(1) The home-based training program consists of individually tailored aerobic exercise on a cycle ergometer. Patients will be supplied with a cycle ergometer, a log book with training instructions and a training scheme at home. Heart rate will be continuously measured with a heart rate monitor. Furthermore, in the log book patients will document the number and duration of treatment sessions, the training load, perceived exertion on the Borg Rated Perceived Exertion Scale [23] and possible complaints after the training session. Training intensity will be gradually increased from 60% of the Heart Rate Reserve (HRR) to 70% HRR, in accordance with the American College of Sports Medicine guidelines for aerobic training in healthy adults [24] and persons with chronic diseases and disabilities [25]. The duration of the training sessions will gradually be increased from 20 to 30 minutes per session and sessions are divided into prescribed exercise bouts which are interspersed with short rest periods of unloaded cycling. The duration of exercise bouts will be gradually increased from 2 minutes at the start of the program to 13 minutes at the end of the program.

Warming-up and cooling-down consists of 5 minutes unloaded cycling. Feasibility of the training schemes is weekly checked by one of the therapists by reading out the heart rate monitors and checking the log books. When necessary, adjustments to the training schemes will be made.

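### One of the two adverse-event capture routes exists only in the therapy arms, so event counts by arm carry ascertainment bias

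*Protocol article*

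**What the plan says.** The Adverse events section names two ways in which an event reaches the trial record: "All adverse events reported spontaneously by the participants or observed by the therapists will be recorded". It adds that events are followed until they resolve or stabilise. It gives no other route.

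Other sections of the protocol article show who has a trial therapist:

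- **Exercise arm** (Exercise therapy): "The intervention has a duration of 16 weeks", with "supervised group training consisting of muscle strengthening and functional exercises once a week". There are also three home sessions a week, with a log book in which patients note "possible complaints after the training session". A therapist checks the log books weekly.
- **CBT arm** (Cognitive behavioural therapy): 12 to 16 one-hour sessions over 4 months.
- **Usual care**: Randomization and blinding says that the patient is told the allocation and, "in case of allocation to exercise therapy or CBT also the therapist of the group allocation". No therapist is mentioned for the third arm. The Usual care section says "Usual care for PPS patients may include usage of assistive devices, orthoses, physical therapy, and medication", but does not say that anyone providing such care reports events to the trial.

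Table 3 lists the instruments used at T1 to T4. None is an adverse-event question or form.

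**The concern.** Therapist observation is tied to allocation. A patient in either therapy arm is seen repeatedly by someone whose observations count as adverse-event data, and a usual-care patient is not. The two therapy arms differ as well, because only the exercise arm has a written prompt for complaints. Even if the true event rates were equal, the recorded counts would be expected to be higher in the therapy arms.

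This matters because safety of exercise is an open question in the article itself. The Background reports that patients are warned off overuse and intensive training because "this could worsen symptoms such as muscle weakness and fatigue and provoke a further loss of muscular strength". It also says that the earlier exercise studies were of insufficient or limited quality. With the planned capture, an excess of events in the exercise arm could be detection alone, and a real excess could be dismissed as detection.

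**Working it through.** **1. The plan's own figures.** The article gives no figure for adverse events. The only plan number needed is the arm size. With 24 per group and 10% drop-out, 24 / 0.90 = 26.7, so 27 per arm, and 3 × 27 = 81, as stated.

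**2. Planned opportunities for capture during treatment.**

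| Arm | Trial therapist sessions | Prompted written record |
|---|---|---|
| Exercise | 16 weeks × 1 = 16 | up to 16 × 3 = 48 log-book entries, checked weekly |
| CBT | 12 to 16 | none described |
| Usual care | none described | none described |

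The assessments T1 to T4 are common to all arms and carry no listed adverse-event item. Spontaneous reports can be made there. However, patients are told at the start of each assessment not to reveal their allocation, which may discourage mention of training-related complaints.

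**3. What unequal capture does to the recorded ratio.** Let *p* be the true proportion of patients with an event, equal in all arms. Let *s* be the share reported spontaneously, and *t* the share of the remainder that a therapist catches.

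- Recorded risk, usual care: *p* × *s*
- Recorded risk, therapy arm: *p* × [*s* + (1 − *s*) × *t*]
- Recorded ratio: 1 + (1 − *s*) × *t* / *s*

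The true risk *p* cancels, so the ratio depends only on *s* and *t*. The documents give neither. The values below are assumptions, with *p* = 30% used only to show patient numbers out of 27.

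| *s* | *t* | Usual care | Therapy arm | Patients of 27 (usual care v therapy) | Ratio |
|---|---|---|---|---|---|
| 0.70 | 0.50 | 21% | 25.5% | 5.7 v 6.9 | 1.21 |
| 0.50 | 0.50 | 15% | 22.5% | 4.0 v 6.1 | 1.50 |
| 0.50 | 0.80 | 15% | 27% | 4.0 v 7.3 | 1.80 |
| 0.30 | 0.80 | 9% | 25.8% | 2.4 v 7.0 | 2.87 |

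The ratio rises with *t* and falls with *s*, so the first and last rows are the extremes of the assumed range: about 1.2 to 2.9 with no true difference.

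**4. Limits of the illustration.** It takes spontaneous reporting to be equally likely in all arms and ignores the log book, which would widen the gap for exercise. It applies to the treatment period. No therapist contact is described after T2, so counts over the whole study would be less distorted.

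**The case against.** Four points can be made in the plan's defence.

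- **Much of the harm feared from exercise is measured symmetrically.** Table 3 has CIS-fatigue, neuromuscular capacity (including quadriceps strength), pain and serum creatine kinase at T1 to T4 in all arms, and outcomes are assessed by blinded assessors. This stands, and it narrows the point. A reader might infer that the harm question cannot be answered at all. The documents do not support that, because worsening on these measures can be compared between arms, provided that the exercise arm's two extra creatine kinase samples at 5 and 10 weeks are left out. Discrete or transient events, such as an injury or a fall, remain uncovered.
- **No between-arm comparison of adverse events is announced.** None of the five research questions asks for one, and Statistical Analyses plans no such test. This also stands. Even so, events tabulated by arm will be read comparatively, and analysis cannot recover events that were never elicited.
- **Usual-care patients are not cut off from the trial.** A reader might infer that they have no trial contact between T1 and T2. The article does not say so: co-interventions are monitored throughout, and cost diaries are listed without restriction by arm. Neither is described as a source of adverse events, so the supportable statement is that no scheduled trial therapist contact is described.
- **An article condenses a fuller protocol.** A standard adverse-event form may exist there, and its absence here is not itself the finding. The finding is that the routes the article does state are unequal by arm.

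**Conclusion.** The point holds in a limited form. As written, the plan makes the chance of recording an adverse event depend on the arm, and by-arm counts cannot be compared without ascertainment bias. The direction, towards more recorded events in the therapy arms, follows from the described contacts if spontaneous reporting is similar across arms. The size is not known from the documents: a ratio of about 1.2 to 2.9 under no true difference rests wholly on the assumed capture rates. A reader might take one pair of rates and speak of a false doubling, but that would be one choice within a wide range whose lower end is small.

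The efficacy comparisons, the sample size and the repeated physiological and symptom measures are unaffected. This is an inexpensive improvement to data collection, not a flaw that undermines the trial.

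**What to change.** Put the same standard adverse-event question to all three arms at the existing T2, T3 and T4 assessments, on a self-completed form that does not pass through the blinded assessors. State that any between-arm comparison of adverse events rests on those answers. Continue to record therapist-observed and log-book events, but label each event by source and report these separately as descriptive data.

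The cost is one short form at each of three visits, with no new visit and no change to the sample size. There are two limits. Recall over about 4 months to T2, and about 3 months to each of T3 and T4, will lose some transient events. Patients also know their allocation, so the form equalises the opportunity to report but not necessarily the inclination. The form has to be in place before the visits take place, because the answers cannot be collected reliably afterwards.

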#### Responsive evaluation

To gain insight into patients' and therapists' expectations of and experiences with both interventions, a responsive evaluation will be conducted [35,36]. Therapists and a subgroup of patients will be interviewed about their experiences with the intervention. The selection of respondents will be based on the criterion of ''maximum variation" [37]. The interviews are semi-structured, with open questions guided by a topic list. In order to check the topic list three pilot interviews will be conducted with patients and one with a partner. Then patients engaged in both interventions will be interviewed. Additionally focus groups will be organized to validate, deepen and broaden the issues in the interviews, starting with two homogeneous focus groups (converging interests) with patients and partners, and two homogenous focus groups with therapists (one per intervention). Then all parties will be brought together in a heterogeneous (diverging interests) dialogue group to exchange views. In the cyclic process data from earlier phases will be used as input for the next phase; this hermeneutic dialectic interaction prevents one-sidedness and fosters the validation of data [38]. During all phases the interviews and focus groups will be tape-recorded, transcribed and analyzed. The analysis will focus on the recurring issues and concerns of all parties, and the comparison of perspectives. Member checks will be held to check the credibility of the analysis [37]. In order to consult and gain advice from patient representatives with PPS the research team will collaborate with the Vereniging Spierziekten Nederland (Dutch patient support group), in all phases of the research process [39].

#### Economic evaluation

Cost-effectiveness and cost-utility will be evaluated from a societal perspective. The costs will include direct health care costs of visits to general practitioners, medical specialists, therapists, medications and assistive devices, direct non-health care costs i.e. non-reimbursable costs for complementary medicine and over-the-counter medication, and indirect, non-health care costs of changes in paid and unpaid work. All these data will be collected via cost diaries.

Resource use will be valued following the procedures outlined by the Dutch Manual of Costing [40]. Where standard cost prices are not available, tariffs or professional fees will be used to estimate costs. The costs of medications will be estimated using the prices reported by the Royal Dutch Society for Pharmacy. Productivity loss costs from paid work will be estimated using both the human capital approach and friction cost method. The productivity loss costs from unpaid work will be determined using a shadow price. Cost prices of the interventions will be determined by a bottom-up calculation.

The effect measures used in the economic evaluation will be our primary outcome measure fatigue and HRQoL measured with the EuroQol-5D [41] at the four different time measurements. Utilities will be derived using the Dutch tariffs and used to determine quality-adjusted life years (QALYs) [42,43].

### Statistical Analyses

GEE (generalized estimated equations) analyses will be used to investigate differences in the effects (primary and secondary outcomes) between both intervention groups and the usual care group and to investigate associations between potential effect modifiers and effect of interventions. Data will be analyzed according to the intention-to-treat principle. Missing data will be imputed by carrying the last observation forward.

The economic evaluation will also be performed according to the intention-to-treat principle. First, mean differences in QALYs will be tested using parametric tests, and uncertainty expressed by 95% confidence intervals. Second, we will conduct between-group comparisons of the mean costs for each of the resource use categories and total costs. Confidence intervals around the mean cost differences will be obtained by a bias-corrected and accelerated (Bca) bootstrapping based on 5000 replications [44]. Third, the incremental cost-effectiveness ratio (ICER) will be determined by dividing the mean difference in total costs by the mean difference in effects. Insight into the uncertainty around the mean ICER will be obtained by bootstrapping based on 5000 replications, the generation of cost-effectiveness planes [45] and cost-effectiveness acceptability curves [46]. Sensitivity analyses involving the most important cost drivers will be performed in order to assess the robustness of the results.

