### Study population

All patients will be recruited from outpatient clinics of the AMC Amsterdam; the University Medical Centre Utrecht (UMCU); the University Medical Centre Nijmegen (UMCN) or the affiliate rehabilitation centres. Case histories are checked to screen for potentially eligible patients. Patients willing to give signed consent are evaluated by a physician to check in and exclusion criteria (Table 1). The sample size was calculated for this three-arm trial based on the comparison treatment (exercise therapy or CBT) versus usual care, with equal allocation across treatment arms and 4 repeated measurements (at entry (pre-treatment), at 4 months (post-treatment), at 3 months follow-up (short-term follow-up) and at 6 months follow-up (long-term follow-up), respectively), with an estimated correlation coefficient of the repeated measurements of rho = 0.79 (based on unpublished data from a reproducibility study in 37 PPS patients), a clinical relevant improvement of 8 points on the CIS-fatigue scale (for both treatments) [17] and an estimated standard deviation in each treatment group of 9.3. The total sample size needed to detect this difference on a 5% level of significance (two tailed) with a power of 90% was 24 subjects in each group [21]. We expect a drop-out rate of maximal 10%, based on a previous trial in this patient group [22]. Therefore 81 patients will be recruited.

**Table 1 T1:** In- and exclusion criteria

Inclusion criteria
(1) diagnosis of PPS according to the criteria of March of Dimes [1]

(2) severe perceived fatigue (CIS-fatigue > = 35) [47]

(3) age between 18 and 75 years

(4) life-expectancy longer than one year

(5) walking-ability at least indoors with or without a walking aid

(6) ability to cycle on a cycle ergometer against a load of at least 25 Watt

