(2) The supervised group training consists of individually tailored muscle strengthening exercises and functional exercises in 1-hour group sessions. Sessions will be divided into a 5-minute warm-up period of aerobic exercises, 30 minutes of muscle strengthening, 20 minutes functional exercises and a 5-minute cool-down period. Muscle strengthening exercise selection and dosage will be determined by the therapist at a separate visit to the treatment location before the start of the program. Muscle groups and accompanying exercises will be selected based on patients MRC-scores [26] and reported problems in daily activities. Exercises are selected based on the best expected effects on physical functioning.

Muscle groups with MRC scores less then 3 are not selected and quadriceps muscles are always selected when this muscle group has a MRC score of at least 3. Training load will be based on the 1-RM test [27]. In the first 4 weeks, training load will be 50% of 1-RM, each exercise consists of 3 sets with 2 minutes rest between a set and number of repetitions will be increased from 8 to 20 during 4 weeks. When the desired number of repetitions with the current load is reached, training load is increased in week 5 and 9 to 60 and 70% respectively, and the number of repetitions is increased in the same manner as prescribed for the first 4 weeks [28].

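### Exercise therapy is partly group-delivered, but neither the sample size nor the stated GEE allows for correlation within training groups, so the standard error for exercise versus usual care may be too small.

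*Protocol article*

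**What the plan says.** All references are to the protocol article.

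- **Analysis.** Under Statistical Analyses, "GEE (generalized estimated equations) analyses will be used" to compare each intervention group with usual care on primary and secondary outcomes, by intention to treat and with last observation carried forward. The section gives no clustering unit, working correlation, standard-error estimator or reference distribution, and no term for training group.
- **Exercise delivery.** Under Exercise therapy, the 16-week programme combines home cycling three times a week with one supervised session a week. On the latter: "The supervised group training consists of individually tailored muscle strengthening exercises and functional exercises in 1-hour group sessions". Group size is not given.
- **Other arms.** Usual care involves no study-organised groups. CBT is customised to the individual and is not described as group therapy.
- **Sample size.** Under Study population, the inputs are "a clinical relevant improvement of 8 points on the CIS-fatigue scale", "an estimated standard deviation in each treatment group of 9.3" and "an estimated correlation coefficient of the repeated measurements of rho = 0.79", "with equal allocation across treatment arms and 4 repeated measurements". The result, "on a 5% level of significance (two tailed) with a power of 90% was 24 subjects in each group", becomes 81 patients after allowance for 10% drop-out.
- **Randomisation.** It is stratified per centre. Compliance and attrition records sessions attended; the article mentions no identifier for the training group.

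**The concern.** Patients who train together each week share a physiotherapist, a location and each other's company. Any effect of these on fatigue is common to the group and makes its members' outcomes correlated. The comparator has no such structure, so the design is partially nested: one arm is clustered and the other is not. Stratifying by centre does not deal with this, because centre cuts across the arms while a training-group effect arises after randomisation and only among exercise patients.

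A model that treats all patients as independent leaves the between-group variance out of the standard error. Intervals are then too narrow and the test rejects too often. The contrast affected is the first research question, exercise therapy versus usual care. A lesser point applies to both contrasts: each has 27 patients per arm recruited and 24 after planned drop-out, which is few for a GEE that relies on large-sample inference, should the default be used.

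**Working it through.** **1. The plan's own figure.** Inputs from Study population: difference 8, SD 9.3, rho 0.79, four measurements, two-sided 5%, power 90%.

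n = 2[SD(z₀.₉₇₅ + z₀.₉₀)/δ]² × [1 + (T−1)ρ]/T

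= 2[9.3 × (1.960 + 1.282)/8]² × (1 + 3 × 0.79)/4 = 28.40 × 0.8425 = 23.93, rounded up to 24.

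Then 24/0.9 = 26.7, rounded up to 27 per arm; 27 × 3 = 81. Both stated figures reproduce from the within-patient correlation alone, so no design effect for training groups is hidden in them.

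**2. Clustering in the exercise arm only.** With group size m, DE = 1 + (m−1) × ICC. The exercise arm's variance is multiplied by DE and the usual-care arm's by 1, so the true standard error is sqrt[(DE + 1)/2] times the one computed under independence. The actual type I error is 2[1 − Φ(1.96/inflation)].

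Assumptions, not in the document: m = 4; ICC 0.02 or 0.05; analysis of the mean of the three post-baseline measurements, adjusted for baseline. The answer depends on the scale of the ICC. With baseline adjustment the residual variance of that mean, as a share of total variance, is (1 + 2 × 0.79)/3 − 0.79² = 0.860 − 0.624 = 0.236. Baseline cannot remove a group effect that arises after randomisation, so a component of 0.02 or 0.05 of total variance becomes 0.02/0.236 = 0.085 or 0.05/0.236 = 0.212 on the analysed scale.

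| Group component | ICC on analysed scale | DE | SE inflation | Type I error, formula |
|---|---|---|---|---|
| 0.02, baseline-adjusted scale | 0.020 | 1.060 | 1.015 | 5.4% |
| 0.05, baseline-adjusted scale | 0.050 | 1.150 | 1.037 | 5.9% |
| 0.02 of total variance | 0.085 | 1.254 | 1.062 | 6.5% |
| 0.05 of total variance | 0.212 | 1.636 | 1.148 | 8.8% |

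Simulation of a t-based ANCOVA that ignores the groups, and so isolates clustering from the small-sample issue, gives about 5.4% to 5.7% for the first pair and 6.6% to 8.5% for the second. This agrees with the formula.

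**3. Wider assumptions, with the plan's own variance and the ICC on the analysed scale.**

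| m | ICC | SE inflation | Type I error | Power at 24 per arm | Evaluable per arm for 90% | Total, 10% drop-out |
|---|---|---|---|---|---|---|
| 3 | 0.01 | 1.005 | 5.1% | 89.8% | 25 | 84 |
| 5 | 0.05 | 1.049 | 6.2% | 87.2% | 27 | 90 |
| 9 | 0.10 | 1.183 | 9.8% | 78.3% | 34 | 114 |

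**4. Small-sample GEE inference, no clustering.** In 20,000 simulated trials with an exchangeable, baseline-adjusted GEE, an uncorrected sandwich with a normal reference rejects in about 6.2% of null trials at 27 per arm and 6.4% to 6.5% at 24. A leverage-corrected sandwich with a t reference rejects in about 4.3% to 4.7%. One three-arm model rather than two pairwise models changes this little (6.15% against 6.2% at 27 per arm).

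**5. Both together.** With groups of 4 and the uncorrected sandwich, the exercise contrast comes to about 6.8% to 7.2% with the ICC on the baseline-adjusted scale, and about 8% to 10% with it as a share of total variance.

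**The case against.** The strongest reply is that the article is silent rather than wrong on most of this. Clustering unit, variance estimator and reference distribution are details that a condensed article normally leaves to the analysis plan. A reader might infer that the GEE is fixed to count only within-patient repeats and to use large-sample standard errors; the text does not say so. That reply stands for the small-sample part, which is conditional on a default the authors may not use. It does not dispose of the sample size, which the article fixes and which demonstrably contains no group-level term.

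A second reply is that the grouping is thin. One session in four each week is in a group, the exercises are individually tailored, and the primary outcome is self-rated fatigue measured up to six months after treatment. This stands as a reason to expect a small ICC, but it does not make the ICC zero.

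Third, a reader might infer that intervals are too narrow in both contrasts because of clustering. The document describes no group delivery for CBT, so that does not follow. CBT patients may share a therapist, as exercise patients do, but that is a separate therapist effect, not a training-group effect.

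Finally, the 8% to 10% figures can mislead. They include the small-sample excess and take the group component as a share of total variance, which is a much larger ICC once baseline is adjusted for.

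**Conclusion.** The point holds in limited form. For exercise versus usual care, the stated sample size omits the partial nesting and the stated analysis names no term for it, so the standard error is too small if outcomes within a training group are correlated. With groups of 4 and an ICC of 0.02 to 0.05, clustering alone gives a type I error of about 5.4% to 5.7% (ICC on the baseline-adjusted scale) or 6.6% to 8.5% (share of total variance). Group size, ICC and baseline adjustment are all assumptions. The effect could be negligible, and becomes material with larger groups or a larger ICC.

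Separately, and only if an uncorrected sandwich with a normal reference is used, the type I error is about 6.2% in both contrasts. The documents do not support saying that the intervals will be too narrow as a matter of fact, or that clustering touches the CBT contrast.

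**What to change.** 1. Record each exercise patient's training group while the trial runs, since it may not be recoverable later.
2. Add a sensitivity analysis for exercise versus usual care with a group effect in the exercise arm only.
3. State the inference method: GEE with a small-sample-corrected sandwich (for example Mancl-DeRouen) and a t reference, or an equivalent linear mixed model fitted by REML with Kenward-Roger degrees of freedom.

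The cost is one recorded identifier, a few lines of analysis text and slightly wider intervals. Baseline adjustment should not be counted as compensation for the wider intervals, because the baseline-adjusted simulations above already include it.
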